## Abstract

**Background:**

UK Hospital Episode Statistics 2013–2014 recorded 57,286 fractures of the lower limb including the ankle. This figure is expected to continue to increase due to a greater population of older adults. Following an ankle fracture, patients usually have their ankle immobilised with a plaster cast. This provides maximum support for the healing ankle but is associated with stiffness and muscle wasting. A Cochrane Review has concluded that functional bracing may reduce muscle wasting and speed recovery of ankle movement.

The aim of this study is to determine the feasibility of conducting a full randomised controlled trial in adults with an ankle fracture followed by functional bracing and exercises versus standard plaster cast care.

**Methods:**

This is a single-centre feasibility randomised controlled trial. All patients with a fractured ankle are potentially eligible. The trial will employ 1:1 random allocation, stratified by age and non-operative/operative management. Baseline demographic and pre-injury functional data, the Manchester-Oxford Foot and Ankle Questionnaire (MOXFQ) and Olerud and Molander Ankle Score (OMAS) will be collected alongside the EuroQol EQ-5D-5 L health-related quality of life questionnaire. A research associate will perform a clinical assessment and obtain X-rays in 6 weeks and 6 months post randomisation to record complications. Functional outcome and health-related quality of life will be collected in 6 weeks, 3 and 6 months post randomisation.

**Discussion:**

This feasibility trial will provide authoritative high-quality evidence to inform the design of a definitive trial in this important area.

**Electronic supplementary material:**

The online version of this article (doi:10.1186/s40814-017-0125-z) contains supplementary material, which is available to authorized users.

## Background

UK Hospital Episode Statistics 2013–2014 recorded 57,286 fractures of the lower limb including the ankle, affecting between 107 and 187 per 100,000 persons [1, 2]. The short-term impact of this injury results in physical impairments, including pain, stiffness, weakness and swelling. The longer-term impact often includes prolonged time off work, development of post-traumatic arthritis and psychological consequences of depression and anxiety [3].

The main bones of the ankle are the talus (in the foot) and the tibia and fibula (in the leg). Distally, the tibia and fibula are bound by a fibrous band called the syndesmosis and have ligament attachments on the inside of the ankle (deltoid ligament) and outside of the ankle (lateral collateral ligaments) which are important for ankle stability. Ankle fractures that occur below the level of the syndesmosis are usually managed with functional braces. Ankle fractures that occur at the level of the syndesmosis can lead to instability, with some requiring open reduction and internal fixation (ORIF) with the aim of restoring stability [3].

For ankle fractures that occur at the level of the syndesmosis, regardless of the decision to operate or not, the immediate rehabilitation has traditionally been plaster cast immobilisation and non-weight-bearing for several weeks. A cast provides maximum support; however, there are potential problems including the immediate impact on mobility for a period of around 6 weeks and risks associated with prolonged immobilisation such as muscle atrophy, deep vein thrombosis and joint stiffness. There are also long-term consequences, which can include prolonged gait abnormalities, persistent calf muscle weakness and an inability to return to previous activity levels. Alternative functional bracing may potentially address these issues [4]. However, it does not provide the same degree of support to the healing bones [3].

This topic was addressed by a Cochrane Review in 2012 [5]. It concluded that functional bracing may improve functional outcome, pain and improve ankle movement. However, these potential advantages needed to be balanced against the increased incidence of adverse events. Consequently, future research was recommended to confirm the clinical and cost-effectiveness of functional bracing following an ankle fracture [5]. In light of the large personal and societal cost associated with the injury, this gap in the evidence is a clear priority.

In 2010, an orthopaedic trauma network (AOUK) undertook a research priority exercise [6]. One of the top priority questions was to establish if there is a clinical advantage to wound healing and ankle function of different rehabilitation plans following an ankle fracture.

The aim of this feasibility trial is to derive sufficiently precise estimates of unknown study population parameters (e.g. outcome variability) such that the feasibility of conducting a full randomised controlled trial (RCT) can be determined. The full RCT will assess the difference in the Manchester-Oxford Foot and Ankle Questionnaire (MOXFQ) in 6 months after injury between adults with an ankle fracture followed by functional bracing and exercises versus standard plaster cast care.

## Methods

### Research question

Is it feasible to conduct a full RCT to assess the difference in the MOXFQ in 6 months after injury between adults with an ankle fracture followed by functional bracing and exercises versus standard plaster cast care?

### Objectives

Evaluate the distributional properties of the MOXFQ in order to estimate the likely sample size required for a full RCTEvaluate the number of eligible patients within the recruiting siteEvaluate the willingness of clinicians to recruit participants (the proportion of eligible patients who are offered participation in the study)Evaluate the willingness of participants to be randomised (the proportion of eligible patients who agree to participate in the study)Evaluate the follow up and response rates to questionnairesRefine the statistical analysis plan to provide the most efficient and sensitive analysisTo discuss the feasibility trial at a national consensus meeting to inform the design of a full RCT

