### Feasibility outcomes

Link to objectives 3, 4 and 5: evaluate the number of eligible patients within the recruiting site; evaluate the willingness of clinicians to recruit participants (the proportion of eligible patients who are offered participation in the study); evaluate the willingness of participants to be randomised (the proportion of eligible patients who agree to participate in the study).

As part of the trial processes, designated research associates will attend daily trauma meetings and fracture clinics held at the trial site. At these locations, they will identify potentially eligible patients who will be entered on a screening log. These logs will contain details of every patient who attends the trial site with an ankle fracture. The TMG will then monitor the number of screened patients who were eligible and offered participation for the trial and the number offered the trial who agree to participate.

Link to objective 7: to discuss the feasibility trial at a national consensus meeting to inform the design of a full RCT.

All the above outcomes will be discussed at a national consensus meeting to discuss more fully with patient, clinician and research representatives the feasibility of conducting a full RCT.

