## Sample size

As this is a feasibility study, a formal power analysis for the sample size will not be undertaken, as the study is not designed to test a specific null hypothesis and infer significance to any observed treatment differences. Instead, we adopt a more informal approach, based on the aims of (i) assessing the distributional properties of the MOXFQ (specifically the variance) and (ii) assessing the likely participation rate (the proportion of eligible patients who are likely to agree to participate in the study). For the first aim, 50 participants in total, 25 in each arm, will be analysed. A sample size of 50 will allow us to estimate a participation rate of 75% to within a 95% confidence interval of ±12%. The data obtained from this study will inform the power analysis for the full study [11, 12].

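### Patients' willingness to be randomised is measured among all eligible patients, not those offered the trial, so it also absorbs clinicians' decisions not to offer it

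*Protocol article*

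**What the plan says.** The Objectives section separates clinicians from patients. The clinician objective, third in that list, is repeated under Feasibility outcomes as "evaluate the willingness of clinicians to recruit participants (the proportion of eligible patients who are offered participation in the study", that is, offered/eligible. The patient objective, fourth in the list, is "Evaluate the willingness of participants to be randomised (the proportion of eligible patients who agree to participate in the study", that is, agreed/eligible. Feasibility outcomes repeats this definition too, although it numbers the objectives differently, so they are named here by content.

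The same section then says that the trial management group will follow the "number of screened patients who were eligible and offered participation for the trial and the number offered the trial who agree to participate".

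The Sample size section uses agreed/eligible as one of its two aims, "assessing the likely participation rate (the proportion of eligible patients who are likely to agree to participate in the study", and gives the precision: "A sample size of 50 will allow us to estimate a participation rate of 75% to within a 95% confidence interval of ±12" percentage points.

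The Discussion names clinicians' willingness as a key driver of future feasibility alongside patients' willingness. It also states that no qualitative work on barriers to enrolment could be included.

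**The concern.** Two quantities with different names share one denominator. Someone who was eligible but never offered the trial stays in the denominator of the patient measure and can never enter its numerator. That person is in effect scored as not willing, although nobody asked. The patient measure therefore carries the clinician measure inside it as a factor.

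This matters because the feasibility rates are a main product of this trial. With no qualitative component, they are the main planned evidence on where recruitment fails. Clinicians not offering the trial and patients declining it call for different responses in the full RCT. A low figure under the heading of patient willingness could be read as refusal when the cause lies with the offer.

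**Working it through.** **Inputs.** Let E be the number eligible, O the number offered the trial and A the number who agree.
- Clinician willingness = O/E (Objectives; Feasibility outcomes).
- Patient willingness as defined = A/E (same sections).
- Planning figure 75%, n = 50, ±12 points (Sample size).
- Offer rate O/E: not given in the protocol, so assumed over 50% to 100%.
- Acceptance among those offered, A/O: not given, so set at 75% for illustration.

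**Step 1: the plan's own figure.** Half-width = 1.96 × √(0.75 × 0.25 / 50) = 1.96 × 0.0612 = 0.120. The ±12 points is reproduced. The formula uses only 0.75 and 50, so it gives the same answer whichever rate the 75% stands for. It is not in dispute here.

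**Step 2: the identity.** A/E = (O/E) × (A/O). The defined patient measure equals acceptance among those offered only when O/E = 1.

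**Step 3: size of the effect, with A/O held at 75%.**

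| Assumed offer rate O/E | Measure as defined, A/E | Shortfall against A/O |
|---|---|---|
| 100% | 1.00 × 0.75 = 75.0% | 0 points |
| 90% | 0.90 × 0.75 = 67.5% | 7.5 points |
| 80% | 0.80 × 0.75 = 60.0% | 15 points |
| 70% | 0.70 × 0.75 = 52.5% | 22.5 points |
| 60% | 0.60 × 0.75 = 45.0% | 30 points |
| 50% | 0.50 × 0.75 = 37.5% | 37.5 points |

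Patients behave identically in every row. The whole shortfall comes from the offer rate.

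**Step 4: the reverse reading.** The Sample size section attaches 75% to A/E. Then A/O = 0.75 / (O/E), which is 0.75/0.90 = 83.3% at a 90% offer rate, 0.75/0.80 = 93.8% at 80%, and 100% at 75%. Below a 75% offer rate, A/E of 75% cannot be reached.

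**Step 5: can the conditional rate be recovered?** Yes: A/O = (A/E) / (O/E). In the 60% row, 0.45/0.60 = 0.75.

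**The case against.** The best defence has several parts, and most of it stands.

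- **No contradiction between sections.** A reader might infer that the protocol gives patient willingness two denominators, because Feasibility outcomes refers to "the number offered the trial who agree to participate". The text does not support this. That phrase is a count and defines no rate. Everyone who agrees must have been offered the trial, so it is the same numerator. Wherever a proportion is written out (Objectives, Feasibility outcomes, Sample size, Discussion), the base is eligible patients.
- **The two drivers can be separated.** A reader might infer that the trial could not tell clinician reluctance from patient refusal. Step 5 shows that it could, because both rates share a denominator. The Participants section also has the screening logs record how many patients were unwilling.
- **The 75% is already attached to a named rate.** The Sample size section ties it to the participation rate, agreed/eligible. That is a legitimate planning quantity for recruitment to a full RCT.
- **The start of an offer is not settled by the text.** The Recruitment section describes a first approach and then full study information. One might infer that the first approach must count as the offer, but nothing there says so.
- **The size is hypothetical.** At a 90% offer rate the shift is 7.5 points, less than the stated ±12. The analysis is descriptive, and the article sets no progression threshold on this rate.

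What the defence does not answer is the definition itself. Being able to derive the right rate from two others does not make the rate reported under the name of patient willingness the right one.

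**Conclusion.** The point holds as a fault of definition. Agreed/eligible is a sound measure of overall recruitment yield but the wrong measure of patients' willingness, because it falls whenever clinicians do not offer the trial. Under an assumed 75% acceptance among those offered, the understatement is 7.5, 15 or 30 points at assumed offer rates of 90%, 80% or 60%, and zero if every eligible patient is offered. The real offer rate is unknown, but the plan treats it as something to be measured.

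One limit applies to either rate: agreed/offered describes the patients who were asked. It describes all eligible patients only if those not asked would have answered similarly. Agreed/eligible would do so only if everyone not asked would have refused.

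The weight is moderate to minor. No data are lost, the plan does not contradict itself, and randomisation, follow-up and the MOXFQ estimates are untouched.

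**What to change.** In the Objectives and Feasibility outcomes sections, define patients' willingness to be randomised as agreed/offered, using the counts that the trial management group already plans to monitor. Keep agreed/eligible under the name of overall participation rate, and leave the 75% planning figure with it as the Sample size section has it. Report three rates side by side, each with its numerator, denominator and 95% confidence interval:

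- clinicians' willingness: offered/eligible;
- patients' willingness: agreed/offered;
- overall participation: agreed/eligible.

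The cost is a change of wording in two sections and one extra line in the feasibility table. It needs no additional patients, visits or data items, and the Sample size calculation stays as it is.

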### Design

This is a single-centre feasibility randomised controlled trial. All patients with a fractured ankle under the care of an orthopaedic consultant in a single UK major trauma centre are potentially eligible. The trial will employ 1:1 random allocation, stratified by age and operative/non-operative management, implemented using a remote, independent telephone randomisation service. A total of 50 participants will be randomised.

All participants will follow a standardised protocol for both treatments. Baseline demographic data and pre-injury functional data using the MOXFQ and Olerud and Molander Ankle Score (OMAS) will be collected alongside the EuroQol EQ-5D-5 L health-related quality of life questionnaire.

A research associate will perform a clinical assessment and obtain X-rays in 6 weeks and 6 months to record any early and late complications. Functional outcome and health-related quality of life will be collected in 6 weeks, 3 and 6 months post randomisation.

### Participants

In standard clinical practise, a patient will first present to the health professional with a history of ‘twisting’ on the ankle or ‘falling’ [2]. The patient will then have an initial X-ray, followed by a discussion with the health professional about their injury that requires surgery and the type of immobilisation required.

In this clinical trial, all adult patients with an ankle fracture for which the treating clinician would traditionally treat the patient in a plaster cast will be considered. In this pragmatic design, this is the primary and most important inclusion criteria. Patients who lack capacity under the Mental Capacity Act 2005, have open ankle fractures, who require close contact casting, have pathological fractures (e.g. known metastatic disease) or any other concurrent lower limb injury that would affect the functional outcome measures (including bilateral ankle fractures and syndesmosis injury requiring surgery) will be excluded.

Screening logs will be collected to assess the main reasons for patient exclusions, as well as the number of patients unwilling to take part. These broad eligibility criteria will ensure that the results of the study can readily be generalised to the wider patient population.

## Intervention and comparator

### All patients

All patients having ankle fixation surgery will have the preferred technique of the operating surgeon. A copy of the ‘operating record’ will form part of the trial dataset, including the grade and experience of the surgeon. All patients will then be placed in a back slab until the stitches are removed 10 days post-operatively, at which point the intervention will be applied.

All patients not receiving surgery will be approached to take part in the trial on first presentation to the trauma team fracture clinic.

### Control group: standard plaster cast

All patients in the control arm will be immobilised with a plaster cast, as per standard practise; the cast may be Plaster of Paris or fibreglass. To monitor compliance, all patients will be asked to complete a daily dairy of how much they bear weight.

### Intervention group: functional bracing

All patients in the intervention arm will be fitted with a removable functional brace. A functional brace is a plastic shell in the shape of a boot, covering the whole foot and leg below the knee, and it has an inner foam liner that is held in place with Velcro. The exact choice of removable functional brace (manufacturer, model, etc.) will reflect the usual hospital stock available, reflecting the pragmatic nature of this study.

Whilst wearing the functional brace, patients will be encouraged to remove their functional brace to complete active unloaded ankle range of movement exercises three times per day, completing ten repetitions on each occasion. To monitor compliance and intervention fidelity, all patients will be asked to complete a daily exercise diary.

Six weeks post treatment, all patients (operative and non-operative) will receive the same standardised, written physiotherapy advice detailing the exercises they need to perform. In this pragmatic trial, any other rehabilitation input beyond the written physiotherapy advice (including a formal referral to physiotherapy) will be left to the discretion of the treating clinicians. However, a record of any additional rehabilitation input (type of input and number of additional appointments) together with a record of any other investigations/interventions will be requested as part of the 3- and 6-month follow-up data.

### Post randomisation withdrawals

Participants may be discontinued from the trial treatment and/or the trial at any time without prejudice. Unless a participant explicitly withdraws their consent, they will be followed up wherever possible and data will be collected as per the protocol until the end of the trial.

### Concomitant illness

Details of any concomitant illness will be recorded at trial entry and all except those outlined in the exclusion criteria are permitted during the trial.

## Outcomes

### Patient-centred outcomes

Baseline data will be collected by the research associates from all participants and will include age, sex, general medical history and pre-injury functional and health status. This will be followed by ascertaining the current function and health status of the patient.

Link to objectives 1 and 6: evaluate the distributional properties of the MOXFQ in order to estimate the likely sample size required for a full RCT. Refine the statistical analysis plan to provide the most efficient and sensitive analysis.

The primary functional status outcome measure for this study is the MOXFQ. Other commonly used foot and ankle scores include the Olerud Molander Ankle Score (OMAS) and American Orthopaedic Foot and Ankle Score (AOFAS); however, they lack a methodologically robust approach in their development, in contrast to the MOXFQ. The MOXFQ is a validated questionnaire which is self-reported (filled in by the patient). It contains 16 items, each with five response options comprising three separate underlying dimensions: walking/standing problems (seven items), foot pain (five items) and issues related to social interaction (four items). Item responses are each scored from 0 to 4, with 4 representing the most severe state. The scale scores representing each dimension are produced by summing the responses to each item within that dimension. Raw scale scores are then converted to a metric (0–100; 100 = most severe) [7]. This will be collected to allow the distributional properties to be evaluated for a later sample size calculation.

Link to objective 2: evaluate the follow up and response rates to questionnaires

The secondary objective measures proposed for the full RCT are health-related quality of life outcome measure for this study is the EQ-5D-5 L. The EQ-5D-5 L is a validated, generic health-related quality of life measure consisting of five dimensions each with a five-level answer possibility. Each combination of answers can be converted into a health utility score. It has good test-retest reliability, is simple for patients to use and gives a single preference-based index value for health status that can be used for broader cost-effectiveness comparative purposes [8]. Although cost-effectiveness analysis is not being carried out as part of this study, it is planned to be included in the definitive study. The methods will adhere to the recommendations of the NICE reference case, which included collection of EQ-5D-5 L. A record of all complications will also be included. The team will evaluate the proportion of these questionnaires that are completed and returned.

Radiographic evaluation of routine pre- and post-injury X-rays (taken at baseline, 6 weeks and 6 months after the injury) will also be collected from the trial team. Standard measurements of joint congruence, fracture angulation, fibular shortening and subluxation will be assessed [9]. We will again evaluate the proportion of these returned.

Whilst the exact number of appointments varies, most patients will be kept under review for 6 months as part of normal practise. The trial procedures will therefore mirror usual care with collection of all outcome measures at baseline, 6 weeks and 6 months face to face by a research associate in the follow-up fracture clinic. This will be alongside postal follow up in 3 months post injury. We will use techniques common in long-term cohort studies to ensure minimum loss to follow-up, such as collection of multiple contact addresses and telephone numbers, mobile telephone numbers and email addresses [10]. Refer to Table 1 for participant timeline.

**Table 1 Tab1:** Schedule of enrolment, interventions and assessments

	Enrolment	Allocation	Post-allocation		
Timepoint			6 weeks (±2 weeks)	3 months (±1 month)	6 months (±1 month)
Enrolment					
Eligibility screen	X				
Informed consent	X				
Allocation		X			
Interventions					
Functional brace		X	X		
Plaster cast		X	X		
Assessments					
Demographic data	X				
EQ5D-5 L/MOXFQ/OMAS	X		X	X	X
Complications			X	X	X
Exercise diary			X		
Physiotherapy input			X	X	X
Radiographs		X	X		X

